#### Sample size

The main study center treated 5 HCC patients with PVTT (all VP4) between 2020 and 2022. These patients underwent surgery after using the same neoadjuvant therapy as this trial. All patients achieved good efficacy, with a postoperative MPR of 60% (3/5), and manageable safety profile, supporting this trial. Based on this result, we set the end-point of effective response rate as 60%. We simulated response rates of 10%, 20%, and 30% assumed as pathological effective naturatly before intervention. The recruiting time for whole population of the patients is 24 months, and the last enrolled patient will be followed for 12 months. Two-sided Tests with 80% power is used with type I error set at 0.05, and one-Sample tests for exponential hazard rate is used to calculate sample size. The sample size calculate by PASS software 2021 version is 6, 10 and 18 for an effective response rate 10%, 20% and 30%, respectively. Based on the maximum possible effective response rate as control at baseline, we finally set it as 30% and obtained a sample size of 18 that included 11 events. The final sample size is 20 patients, allowing for a 10% loss to follow-up.

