## Discussion

Portal vein tumor thrombus (PVTT) is a common phenomenon in hepatocellular carcinoma (HCC) patients, classified by the VP classification of Japan (15) or Cheng’s type of China in clinical practice. VP classification appeared earlier and was more widely used worldwide so in this study VP classification will be used as the classification standard of PVTT.

Our protocol explores the safety and efficacy of radiotherapy combined with lenvatinib and PD-1 inhibitor (sintilimab) as neoadjuvant therapy for hepatocellular carcinoma complicated with PVTT, which has good prospects.

First, radiotherapy is an effective treatment modality for PVTT. A previous report pointed out that the response rate of radiotherapy in patients with different PVTT classifications was 32.6%-100%, and the 5-year survival rate and the median OS were 5.1%-58.0% and 5.3 to 27.0 months, respectively (16). Low-dose radiotherapy can enhance immunity, which provides a curative effect in PVTT than liver tumors. A Japanese study performed 30-60Gy/10-12F radiotherapy on the tumor thrombus of the main portal vein and its branches, and then surgical resection was performed within 2 weeks after radiotherapy. The results showed that the postoperative PCR rate reached 53%. Another controlled study in China found that neoadjuvant radiotherapy improved PFS and OS in PVTT patients, with the radiation dose of only 3Gy*6F. Low-dose radiotherapy reducing radiation damage to normal tissues and organs can effectively reduce the incidence of adverse reactions, improving the quality of life. In this study, the radiotherapy dose was determined to be 3Gy*10F.

Second, combined targeted and immune therapy is an effective treatment for HCC, having a synergistic effect with radiotherapy. The improvement of the objective response rate of systemic therapy drugs, such as various anti-angiogenic drugs and immune checkpoint inhibitors (ICIs), has brought more possibilities for preoperative treatment. Moreover, low-dose radiation converts TAM to M1 phenotype, infiltrating existing T cells into tumors, thereby promoting the transformation of tumors from “cold” to “hot” (17, 18). In addition to that, some clinical studies suggested that the combination of radiotherapy and immunization may benefit the survival of patients with unresectable HCC (19, 20).

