Third, a few studies recently have explored neoadjuvant therapy of HCC. The final results of nivolumab alone or in combination with ipilimumab in the perioperative period of resectable HCC, a phase II randomized controlled, open-label study, were reported at the 2020 ASCO meeting. The results demonstrated that among 27 evaluable patients, the pCR rate was 19%, with 21 patients undergoing planned surgery (21). Another study in mildly resectable or locally advanced HCC reported at ASCO-GI 2021 showed that neoadjuvant therapy of cabozantinib combined with nivolumab achieved margin-negative resection in 12 of 15 patients, of which 5 were major/complete pathological response (22).

To date, there are no study on neoadjuvant therapy using lenvatinib and PD-1 inhibitor combined with radiotherapy for BCLC stage C. This study will provide preliminary evidence for the safety and efficacy of radiotherapy combined with lenvatinib plus PD-1 inhibitors (sintilimab) as neoadjuvant therapy for resectable HCC with PVTT. In addition, some interesting questions, such as the PVTT regression rate with neoadjuvant therapy and the consistency of imaging and pathological assessment of PVTT regression rates, will be explored in this study. In summary, this study may supplement the clinical decision-making evidence in the neoadjuvant treatment of BCLC stage C patients.

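### The sample size rests on an unsourced 30% null and a 60% target from five operated patients; its stated 80% power does not hold for MPR, and exceeding 30% would not show a gain over radiotherapy

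*Protocol article*

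**What the plan says.** The Sample size section starts from a small local series: "The main study center treated 5 HCC patients with PVTT (all VP4) between 2020 and 2022". On treatment it adds: "These patients underwent surgery after using the same neoadjuvant therapy as this trial". On outcome: "All patients achieved good efficacy, with a postoperative MPR of 60% (3/5"). The target follows directly: "Based on this result, we set the end-point of effective response rate as 60"%.

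Three candidate nulls were tried: "We simulated response rates of 10%, 20%, and 30% assumed as pathological effective naturatly before intervention". The largest was kept: "Based on the maximum possible effective response rate as control at baseline, we finally set it as 30"%. The stated settings are two-sided type I error 0.05, 80% power and a one-sample test for an exponential hazard rate. They give 6, 10 and 18 patients for nulls of 10%, 20% and 30%. The last of these (11 events) is raised to 20 for 10% loss to follow-up.

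Other parts of the article bear on these inputs:

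- **Outcome definitions:** MPR means at most 10% surviving tumor, and no denominator is stated. Completing treatment and proceeding to surgery is the feasibility endpoint, which is co-primary with safety.
- **Table 1:** the trial admits vp1 to vp4.
- **Table 4:** follow-up is laid out for non-operated patients too.
- **Discussion, radiotherapy:** for a study of 30-60 Gy in 10-12 fractions to the thrombus, then resection: "The results showed that the postoperative PCR rate reached 53"%.
- **Discussion, drug regimens:** one regimen gave 5 major or complete responses, with 12 of 15 patients having margin-negative resection. For another, with 27 evaluable patients: "the pCR rate was 19%, with 21 patients undergoing planned surgery".

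**The concern.** The null decides the sample size: the article's own three scenarios run from 6 to 18 patients on that input alone. Calling 30% the highest possible control rate presents the choice as conservative. Yet the only pathological response rates the article cites for radiotherapy, or for major response under another regimen, lie above 30%.

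The null is also described as the response present without treatment. The trial gives radiotherapy, lenvatinib and sintilimab together, and the article itself calls radiotherapy effective for PVTT. A result above 30% would therefore not say which component produced it.

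The target has a separate weakness. It comes from patients who all had surgery, but the trial enrols patients before surgery is certain. If the denominator is everyone enrolled, each unresected patient lowers the achievable rate. The 10% allowance covers loss to follow-up, not failure to reach surgery.

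At stake is the only stated justification of the sample size. The article also says that these outcomes will be used to size the next study, so a weak benchmark would carry forward.

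**Working it through.** **1. Reproducing the stated figures.** Inputs (Sample size section): rates 30% and 60%, two-sided 0.05, 80% power, 24 months' accrual, 12 months' further follow-up. Assumption needed to reproduce: both rates are 12-month event-free proportions, with hazard h = -ln(rate) per year.

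- h0 = -ln 0.30 = 1.204; h1 = -ln 0.60 = 0.511; ln(h0/h1) = 0.857.
- Events d = ((1.960 + 0.842)/0.857)² = 10.68, so 11.
- P(event) under h1 = 1 - (e^(-h1) - e^(-3·h1))/(2·h1) = 1 - (0.600 - 0.216)/1.022 = 0.624.
- N = 11/0.624 = 17.6, so 18; 18/0.9 = 20.
- Without rounding d first, nulls of 20% and 10% give 9.5 and 5.5, so 10 and 6.

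All stated figures reproduce, but only as a time-to-event calculation. MPR is a yes/no outcome read once on the specimen, so the 80% power does not transfer to it automatically.

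**2. The same comparison as a binary MPR test.** Exact binomial, two-sided 0.05, null 30%, true rate 60%:

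| N | Reject at | Upper tail at 30% | Power at 60% |
|---|---|---|---|
| 18 | 10 or more | 0.021 | 0.74 |
| 20 | 11 or more | 0.017 | 0.76 |

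At N = 20, a count of 10 has upper tail 0.048 and a two-sided minimum-likelihood p of 0.083, so the cutoff of 11 holds under either exact definition. The smallest N reaching 80% is 23. A normal-approximation z test gives 20.

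**3. Precision of the target.** The exact (Clopper-Pearson) 95% CI for 3/5 is 14.7% to 94.7%.

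**4. Effect of non-resection.** Assumption: MPR is 60% among resected patients, and unresected patients count as non-responders. Rate over all enrolled = 0.60 × share resected; power = P(X ≥ 11) with N = 20.

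| Share resected (assumed) | MPR over all enrolled | Power against 30% |
|---|---|---|
| 100% | 60% | 0.76 |
| 90% | 54% | 0.56 |
| 80% | 48% | 0.34 |
| 70% | 42% | 0.17 |

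For orientation only, the cited drug studies give 21/27 = 78% operated and 12/15 = 80% margin-negative resection. These are other regimens, and the second figure is not the share reaching surgery.

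**5. The null beside the cited rates.** 53% (complete response), 5/12 = 42% and 5/15 = 33% all exceed 30%. The cited 19% complete response rate does not, but complete response is narrower than MPR. If the true MPR were 53%, 11 or more of 20 would occur with probability 0.52. An exact test of 53% at N = 20 rejects at 16 or more (upper tail 0.012) and has power 0.05 at a true 60%. Both figures treat the cited 53% as an MPR rate, which the article does not establish.

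**The case against.** The strongest reply is that the 30% is meant as a response rate before any intervention, and the largest of three candidates was taken. A rate observed after radiotherapy does not refute an assumed untreated rate. The aim is to study the combination, and the article never promises to isolate what the drugs add. This stands in part. A reader might infer that beating 30% shows nothing about the combination; the article does not support that, because it could show activity over no treatment.

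Second, the 53% is not like for like. The cited radiotherapy went to the thrombus, with surgery within two weeks; here thrombus and primary tumor are both irradiated and surgery follows 6 to 8 weeks later. The article gives no denominator for the 53% and does not say whether thrombus or whole tumor was assessed, or that radiotherapy was the only preoperative treatment. It is therefore tempting but unsupported to say that radiotherapy alone would beat 30% about half the time. The figure counts against calling 30% a ceiling; it is not a replacement null.

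Third, MPR is secondary in an exploratory phase I trial, and no MPR success rule is stated. The cutoff of 11 of 20 is this review's reading of the stated error rates. The criticism therefore reaches the justification of the sample size and the reading of MPR, not the safety and feasibility conclusions.

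Fourth, the MPR denominator is unstated, and eligibility requires a resectable primary tumor, so the dilution may be small. That is fair, and is why a range is shown. Even with everyone resected, exact power is below 80%, though only slightly.

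The all-VP4 series is a mismatch without a clear direction: VP4 has the shortest recurrence-free survival in the Introduction, so that feature need not make 60% optimistic.

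**Conclusion.** The point holds as a fault in how the sample size is justified. The 30% null has no source, and the article's own citations do not support presenting it as the highest possible rate. The 60% target is five operated patients with an interval from 15% to 95%, applied to a trial in which surgery is not assured.

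For MPR, the stated 80% power is 0.76 at best with 20 patients (0.74 with 18). It falls to between 0.56 and 0.17 if 90% to 70% are resected. Those lower figures rest on three assumptions: 60% among resected patients, unresected patients counted as non-responders, and resection shares that the article does not give for this regimen. The shortfall with full resection is minor; the dependence on resection is what matters.

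Exceeding 30% would be compatible with activity over no treatment but would not show that lenvatinib and sintilimab add to radiotherapy. The primary endpoints are unaffected.

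**What to change.** In the Sample size section:

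- Delete the statement that 30% is the highest possible control rate.
- Either remove the 80% power justification on MPR, or keep a benchmark with a source and state the power that 20 patients deliver by a method suited to a binary outcome.

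In the Outcome definitions and Statistical analysis sections:

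- State the MPR denominator. Report MPR as n/N with an exact 95% CI over all enrolled patients, counting those not resected as not having MPR, and also among resected patients.
- State that this single-arm trial cannot separate the effect of the combination from that of radiotherapy.

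The cost is rewording and a more modest efficacy statement. No extra patients or data are needed.

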#### Statistical analysis

This is an open-label, single-arm, phase I clinical trial and a planned 20 eligible subjects will be enrolled. Descriptive Analysis: The description of the quantitative indicator will give the median. Baseline Demographic Analysis: Descriptive analysis of baseline demographic data, and the chi-square test or survival analysis for numerical data in the experimental and control groups, depending on the data type. Analysis of evaluation indicators: Safety and feasibility, MPR rate, 1-year recurrence-free survival rate, ORR, PVTT regression rate, IPCR, ECOG score, tumor marker changes (AFP, PIVKA-II), ICG-R15 Changes, changes in liver function, etc. analysis of variance using two independent samples t-test, nonparametric test, repeated measures design according to data type. OS and RFS will use survival analysis according to data type. Safety evaluation: Adverse events will be described by the number and incidence, and detailed descriptions of the specific manifestations and degrees of all adverse events and their relationship with the drugs used. Since it is an exploratory study, the research data and results are subject to the investigator’s evaluation, and a Data Monitoring Committee (DMC) is not specially established.

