## Methods and analysis

### Study design

This is an open-label, single-arm, prospective, multi-center phase I trial in HCC patients with portal vein thrombus which will be conducted in 5 hospitals in China. (**Figure 1**). The study is being followed the Declaration of Helsinki and Good Clinical Practice. The protocol and its amendments have been approved by the ethics committee of Beijing Tsinghua Changgung Hospital (No. 21323-0-03). The recruitment started on December 01, 2022. The enrolment is estimated to complete in December 1, 2025.

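### The Statistical analysis section prescribes two-group tests for a single-arm trial and names no one-sample estimate with an interval for its response and feasibility rates

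*Protocol article*

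**What the plan says.** The Study design section states: "This is an open-label, single-arm, prospective, multi-center phase I trial". The Statistical analysis section opens the same way: "This is an open-label, single-arm, phase I clinical trial and a planned 20 eligible subjects will be enrolled".

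That section then sets out two groups of methods:

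- Baseline demographics are to be described, and are also to receive "the chi-square test or survival analysis for numerical data in the experimental and control groups, depending on the data type".
- The evaluation indicators are to be handled by "analysis of variance using two independent samples t-test, nonparametric test, repeated measures design according to data type". The list covers safety and feasibility, the MPR rate, 1-year recurrence-free survival, ORR, PVTT regression, IPCR and ECOG score. It also covers "tumor marker changes (AFP, PIVKA-II), ICG-R15 Changes, changes in liver function, etc".

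Separately, adverse events are to be reported by number and incidence, and OS and RFS by survival analysis.

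The Anticipated results section says that the outcomes will be used to judge whether a phase II study is feasible and to set the sample size of the next study.

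**The concern.** Both named comparisons need two independent groups, and the trial has one. The baseline sentence has a second problem: neither a chi-square test nor survival analysis is a method for numerical baseline variables.

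The sentence on evaluation indicators puts two kinds of outcome under one list of tests. Rates observed in one group of patients call for a one-sample estimate and an interval. Changes between visits in the same patients call for a paired or repeated-measures analysis. An independent-samples t-test fits neither.

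What is at stake is mainly the rates. They are meant to feed the phase II decision, and with 20 patients their uncertainty is wide enough to matter there. The marker and liver-function changes come second, because they are not among the listed primary or secondary endpoints.

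**Working it through.** **1. Is there a second group anywhere?** Two candidates appear, both in the Sample size section.

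- The word control is used for a reference value: "Based on the maximum possible effective response rate as control at baseline, we finally set it as 30" (per cent). This is a fixed number, not a set of patients.
- Five earlier patients at the main centre are described: "These patients underwent surgery after using the same neoadjuvant therapy as this trial". Patients given the same regimen are not controls for it.

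No split of the 20 trial patients into two comparison groups is defined either.

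**2. Which framework does the sample size use?** The target is stated as "we set the end-point of effective response rate as 60" (per cent), with reference rates of 10%, 20% and 30%, two-sided alpha 0.05, power 80%, 24 months of accrual and 12 months of further follow-up. The stated method is a one-sample exponential hazard test. With time in years and h = -ln(rate):

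- h1 = -ln(0.6) = 0.511.
- Events: E = (1.960 + 0.842)² / [ln(h1/h0)]².
- Probability of an event under h1 with uniform accrual: 1 - (e^(-h1) - e^(-3h1)) / (2h1) = 0.624.

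| Reference rate | h0 | E | N = E/0.624 | Stated N |
|---|---|---|---|---|
| 10% | 2.303 | 3.46 | 5.55, so 6 | 6 |
| 20% | 1.609 | 5.96 | 9.55, so 10 | 10 |
| 30% | 1.204 | 10.68, so 11 | 17.11, so 18 | 18 (11 events) |

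Then 18 / 0.9 = 20. The plan's figures reproduce, and they come from a calculation with one group. The Sample size section therefore agrees with the single-arm design, and the Statistical analysis section does not.

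**3. Match each indicator to the listed methods.**

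| Indicator | Type (Outcome definitions; Table 4) | Does a listed method fit? |
|---|---|---|
| Safety | number of patients with an event | Not in the list, but adverse events are separately described by number and incidence; no interval |
| Feasibility | number of patients | No |
| MPR, ORR, PVTT regression, IPCR, 1-year recurrence-free rate | one-sample proportions | No |
| AFP, PIVKA-II, ICG-R15, liver function, ECOG | repeated on the same patients | Repeated measures: yes. Independent-samples t-test: no |
| OS, RFS | time to event | Survival analysis, named separately |

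The missing intervals are wide. If 12 of 20 patients responded (60%), the exact 95% interval would be 36% to 81%.

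**4. What would the independent-samples t-test do to the changes?** Take n = 20 pairs, equal SD of 1 at both visits, normal data and pre/post correlation rho. The documents give no correlation, so rho and the 0.5 SD change are assumptions.

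- Independent SE = sqrt(2/20) = 0.316.
- Paired SE = sqrt(2(1 - rho)/20).
- Ratio of the two = 1/sqrt(1 - rho).

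| rho | SE ratio | True type I error, independent test (nominal 5%) | Power, independent | Power, paired |
|---|---|---|---|---|
| 0.5 | 1.41 | 0.7% | 28% | 56% |
| 0.7 | 1.83 | 0.1% | 25% | 78% |
| 0.8 | 2.24 | below 0.1% | 22% | 92% |

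The independent-test columns come from simulation (200,000 trials per setting). The paired power also follows from the noncentral t distribution with 19 degrees of freedom and noncentrality 0.5 × sqrt(20) / sqrt(2(1 - rho)). At a weaker rho of 0.3 the gap is smaller: power 31% against 44%.

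**The case against.** The strongest reply is that the sentence on evaluation indicators offers three options and leaves the choice to the type of data. Repeated measures is one of them and suits within-patient change. On that reading the plan never assigns the independent-samples t-test to AFP or ICG-R15, and an analyst could follow it correctly. This stands in part: a valid route for the changes is named, but an invalid one is listed beside it, with no rule beyond data type to choose between them. Data type does not settle whether measurements are paired.

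It can also be said that the trial is exploratory, that both primary endpoints are counts needing no test, and that interval methods are detail an article may leave to a fuller document. The first two points are fair and limit the consequence. The third would excuse silence, but the section is not silent: it names tests that the design cannot support.

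A reader might infer more than the text supports:

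- *Every analysis is either impossible or ignores pairing.* The repeated-measures option, the descriptive adverse-event reporting and the survival analysis of OS and RFS contradict this.
- *The primary safety endpoint has no usable analysis.* It is covered by the description of adverse events by number and incidence.
- *The t-test could produce false claims of benefit.* With positive correlation, type I error falls below 5%. The cost is lost power.
- *The control-group wording signals a planned comparison with historical or non-operated patients.* Nothing in the article says so.

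**Conclusion.** The contradiction is certain and rests on no assumption: the Statistical analysis section calls the trial single-arm and then prescribes a comparison with a control group that does not exist. The baseline comparison cannot be run. For feasibility and the five secondary rates, no listed method gives an estimate with an interval, although the outcomes are to inform the next study.

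The loss on the within-patient changes is conditional. It arises only if the independent-samples test is the option chosen, and its size (power of about 22-28% instead of 56-92%) depends on the assumed correlation of 0.5 to 0.8, the 0.5 SD change and normal data. Normality is doubtful for AFP and PIVKA-II on the raw scale, so these figures are an illustration.

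No sample-size figure changes. This should be fixed; it does not undermine the trial.

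**What to change.** Rewrite the paragraph in the Statistical analysis section:

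1. Delete the comparison between experimental and control groups, and the independent-samples t-test.
2. Report baseline data descriptively only.
3. Report safety, feasibility, MPR, ORR, PVTT regression, IPCR and the 1-year recurrence-free rate as n/N with exact 95% confidence intervals. Use a Kaplan-Meier estimate for the 1-year rate if any patient is censored before one year.
4. Analyse changes in tumour markers, ICG-R15, liver function and ECOG score with a paired t-test, a Wilcoxon signed-rank test or a repeated-measures method, and say which applies to which variable.
5. Leave the adverse-event description and the survival analysis of OS and RFS as they are.

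The cost is one paragraph of text. No new data, visits or patients are needed.
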